**Figure 6 fig6:**
[figure not shown]
Acceleration-deceleration curves during light activity. Red and blue represent data from subjects with persistent atrial fibrillation (n=7) and no heart disease (n=15), respectively. The mean and standard deviation are shown per time point (5 second intervals) for both groups.

### MIL can detect healthy cardiovascular outcomes

The peak aligned acceleration-deceleration curves are concatenated with their corresponding step counter data and grouped per week to form bags. The MILES (Multiple-Instance Learning via Embedded Instance Selection) model is then used to classify every week as healthy or AF. The results in Table 2 show that even though the sensitivity is low, the specificity is decent. This shows potential in avoiding unnecessary visits to a cardiologist for patients who have symptoms that are wrongly suspected to be related to heart problems.

**Table 2 tbl2:** Confusion matrix of per-week healthy vs atrial fibrillation classification of the MILES model with peak aligned curves concatenated with step counter data, with true and predicted labels shown vertically and horizontally, respectively

True/Predicted label	AF	Healthy
AF	11	14
Healthy	7	33

AF = atrial fibrillation.

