**Results:**

Enrollment commenced on May 1, 2022, and as of the time of this report, 62 subjects have been included in the study. Preliminary analysis of the data reveals significant inter-subject variability. Notably, we identified heart rate recovery curves and time-delayed correlations between heart rate and step count as potential strong indicators for heart disease.

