### Algorithm validation

In our specific setting where the model encounters data from previously unseen subjects without any prior knowledge, we use leave-p-subjects-out cross-validation (LPSOCV). This approach, shown in Figure 4, ensures a more accurate reflection of real-world situations. LPSOCV involves multiple iterations, or folds, during which data from distinct subjects are used for training and validation purposes (ie, the model is validated on data from subjects that the model is not trained on), mitigating observation bias.

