### Study characteristics

So far, 62 of the 200 envisioned subjects have been included and data from 22 subjects (15 healthy, 7 AF) have been extracted successfully from the data platform for preliminary analysis (Table 1).

**Table 1 tbl1:** Characteristics of preliminary study participants as of May 2022

Characteristic	Ref	HF	AF
Participants, n	25	15	22
Age, y			
18–39	16	1	0
40–54	3	3	2
55–64	5	5	3
65+	1	6	17
Sex			
Male	12	12	15
Female	13	3	7
BMI			
18.5–24.9	14	3	7
25–29.9	6	6	8
30+	5	6	7
Diabetes			
Yes	0	5	4
No	25	10	18
Smoking			
Yes	0	6	5
No	25	9	17
Hypertension			
Yes	2	8	15
No	23	7	7
Device			
Charge 5	23	8	12
Inspire 2	2	7	10

AF = atrial fibrillation group; BMI = body mass index; HF = heart failure group; Ref = reference group.

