### Heart rate peak alignment in acceleration-deceleration curves indicate difference between 7 AF patients and 15 healthy controls

Next, we explored the heart rate recovery curves after activity (acceleration-deceleration curves).^12^ First a peak is detected, whereafter the start (onset) and end (recovery) points associated to that peak are determined by the minimum heart rate value 5 minutes before and 15 minutes after the peak. The curves are preprocessed by aligning the peaks on the time axis. Additionally, for every subject, the amplitude of the curves is rescaled by the average peak value across all curves for that individual. Figure 6 shows the curves for light activity, defined by a maximum of 20 steps in the 5 minutes preceding the peak and fewer than 10 steps in the 15 minutes after the peak. There are 2 noticeable differences in heart rate patterns between persistent AF patients (in red) and healthy participants (in blue). The standard deviation for AF patients is considerably smaller than that of healthy individuals, and their heart rate recovery is slower, as observed at the 6-minute mark. These distinctions could potentially serve as clinical indicators for atrial fibrillation.

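### Table 2 is computed on subjects whose recovery curves had already been compared by diagnosis, so its discrimination may be optimistic unless the curve was fixed beforehand

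*Protocol article*

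**What the plan says.** Results, *Study characteristics*, reports that "data from 22 subjects (15 healthy, 7 AF) have been extracted successfully from the data platform for preliminary analysis". The next analysis of interest is headed "Heart rate peak alignment in acceleration-deceleration curves indicate difference between 7 AF patients and 15 healthy controls", and the caption of Figure 6 confirms who was in it: "Red and blue represent data from subjects with persistent atrial fibrillation (n=7) and no heart disease (n=15), respectively". That section reports two differences between the groups, a smaller spread and a slower recovery in AF, and suggests that they could serve as clinical indicators. The Abstract sums up the preliminary work by saying that "we identified heart rate recovery curves and time-delayed correlations between heart rate and step count as potential strong indicators for heart disease".

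The section on MIL then states the classifier's input: "The peak aligned acceleration-deceleration curves are concatenated with their corresponding step counter data and grouped per week to form bags". MILES labels each week as AF or healthy, and Table 2 gives the counts. The text under that heading calls sensitivity low and specificity decent. The Discussion goes further: it calls the specificity high and presents the result as something the findings demonstrate. It also proposes preselecting windows on patterns such as this curve.

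Methods, *Algorithm validation*, describes leave-p-subjects-out cross-validation, in which "the model is validated on data from subjects that the model is not trained on", and an external test set of 20% of subjects. The article does not say that either was used for Table 2.

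**The concern.** Subject-wise cross-validation protects against one kind of leakage: a model fitted to a subject's data and then tested on that subject. It does not protect against an earlier step in which someone looks at all subjects by diagnosis, sees that a certain curve separates them, and makes that curve the input. Every held-out subject has then already helped to choose what the model sees. The resulting sensitivity and specificity describe performance on the development data, whatever the fold structure.

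Table 2 is the only classification result in the article, and the Discussion rests its statement about ruling out heart disease on it. The same mechanism could carry into the main analysis if windows are preselected on patterns found in labelled subjects who later serve for validation or testing.

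**Working it through.** **1. Overlap of subjects.** Extracted: 7 AF + 15 healthy = 22. In Figure 6: 7 AF + 15 healthy = 22. Table 2 does not give its number of subjects. But with no other AF or healthy data reported as extracted, every subject in Table 2 was also in the labelled comparison, even if Table 2 uses only some of them.

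**2. What Table 2 shows.** The article prints counts and no percentages, so there is no stated figure to reproduce.
- Sensitivity = 11/(11 + 14) = 11/25 = 44.0% (Clopper-Pearson 95% interval 24.4 to 65.1).
- Specificity = 33/(7 + 33) = 33/40 = 82.5% (67.2 to 92.7).
- J = sensitivity + specificity − 1 = 0.440 + 0.825 − 1 = 0.265.
- Accuracy = (11 + 33)/65 = 67.7%. Calling every week healthy gives 40/65 = 61.5%. The margin is 44 − 40 = 4 weeks.

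The intervals treat weeks as independent. The 25 AF weeks come from at most 7 subjects and the 40 healthy weeks from at most 15, so the intervals are probably too narrow.

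**3. How large the optimism could be.** The article does not say how many inputs were considered, so this is a range under assumptions. Data for 7 and 15 subjects were simulated with no true difference. The candidate with the largest group difference was chosen on all 22 labels, and a nearest-mean classifier was then run with leave-one-subject-out validation. There were 1,500 data sets per row for a single feature and 800 for a 20-point curve chosen as a whole.

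| Candidates | J, single feature | J, whole curve |
|---|---|---|
| 1 (fixed beforehand) | −0.03 | −0.05 |
| 2 | 0.16 | 0.05 |
| 3 | 0.23 | 0.08 |
| 5 | 0.28 | 0.14 |
| 10 | 0.34 | not run |

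With one candidate there is no upward bias. With a choice made on all labels, J rises above zero although every subject was held out of fitting. The whole curve is closer to what MILES received, and there the effect at 5 candidates is about half of the observed J (0.14/0.265 = 0.53).

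**4. Would the planned external test set be free of this?** Twenty per cent of 200 is 40 subjects. With equal numbers per class this is 40/3, about 13 each. If all 200 are recruited and the draw is random within class, the expected number of explored subjects in the test set is 7 × 13.3/50 + 15 × 13.3/100 = 1.9 + 2.0, or about 4. The article asks that test subjects be new to the model. It does not say that subjects used to explore the curves are kept out.

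**The case against.** The strongest reply is that the selection step is inferred. The curves are introduced with a literature citation, and no sentence says that they became the MILES input because of Figure 6 or that other inputs were tried and dropped. The second indicator named in the Abstract, the lagged correlation, is presented after Table 2, so it is not evidence of a choice between two. MILES received whole curves with step counts, not the two differences seen in Figure 6, and rescaling by each subject's own mean peak uses no labels. The results are labelled preliminary, and the planned model is to learn its features by self-supervision and face unseen subjects.

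Much of this stands. A reader might infer that the sensitivity and specificity in Table 2 are both biased upward. The documents do not support that: if the curve was fixed in advance this bias is absent, and how any optimism divides between the two measures depends on the threshold. A reader might also note that 5 single-feature candidates give a null J of 0.28, close to the observed 0.265, and conclude that Table 2 is explained by selection. That match depends on assuming one scalar feature, an invented number of candidates and classification of subjects rather than weeks.

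Two things do not fall away. A citation is not the same as a choice fixed before the labels were seen: in the same simulation, a single feature kept only if its group difference reached p < 0.5, 0.2 or 0.05 gave a null J of 0.23, 0.33 or 0.43. The article does not say that such a filter was applied, but neither does it say that the curve was fixed. And the preliminary label does not fit the Discussion's wording, which is stronger than that of the section reporting the result.

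**Conclusion.** The concern holds as a conditional one. The subjects behind Table 2 had already been compared by diagnosis on the same curves, and the article's own summary speaks of the curves as identified in that work. Unless the definition was set beforehand, J = 0.265 may be optimistic even under subject-wise cross-validation.

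The amount cannot be recovered from the article. Under the stated null assumptions it runs from none, through a J of 0.05 to 0.14 for a whole curve among 2 to 5 candidates, to 0.16 to 0.34 for a single feature among 2 to 10. These figures show what the mechanism can do; they do not estimate what happened. What changes is the reading of Table 2: it is a development result that needs confirmation, and it cannot carry the Discussion's statement on specificity. The planned study is not compromised, provided the choice of pattern is kept away from the subjects used to test it.

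**What to change.** 1. Label Table 2 as development performance. State when the curve definition was set, how many inputs were tried and how Table 2 was validated. If the definition preceded the labelled comparison, saying so removes the concern.
2. Reword the Discussion to match the Results, for example: *in development data drawn from 7 AF and 15 reference subjects, whose recovery curves had also been compared by group, MILES classified 33 of 40 healthy weeks and 11 of 25 AF weeks correctly; this needs confirmation in subjects not used to explore the curves.*
3. In the planned analysis, make any label-guided choice of pattern for window preselection inside the training folds, or freeze it before testing. A fixed rule applied without labels may run on all subjects.
4. Draw the external test set from subjects outside these 22. At full recruitment this leaves 50 − 7 = 43 AF and 100 − 15 = 85 reference subjects for about 13 places each, so the test set need not shrink.

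The cost is wording, one restriction on the random draw and a little more analysis work; the quoted performance may become less favourable. An earlier check on the other enrolled subjects (22 − 7 = 15 AF and 25 − 15 = 10 reference in Table 1) is possible but not a simple rerun. Their data must first be extracted. The AF group also admits paroxysmal and permanent AF, whereas Figure 6 shows persistent AF, so a weaker result could reflect AF type. Subjects used in this way should then also stay out of the external test set.

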### Step counter and heart rate are correlated with a time delay

Next, we examined whether the cross-correlation function between the heart rate window and its corresponding step counter window is indicative of heart disease. To calculate the correlation, we consider varying window sizes and time differences (lags) between heart rate and steps. The computed cross-correlation matrix for the healthy group, along with the AF and HF patient groups, as shown in Figure 7, shows that the heart rate is correlated with the step counter with 1-minute delay.

**Figure 7 fig7:**
[figure not shown]
Cross-correlation matrices between windowed heart rate data and number of steps for healthy and the persistent atrial fibrillation (AF) group. Rows are window sizes and columns lag between heart rate and step counter.

## Discussion

By building a suitable infrastructure with Cloud technology, big data acquired in the study is used to develop data-efficient models using methods from multiple instance and self-supervised learning.

We aim to examine the influence of inter-subject variability on predicting cardiovascular disease and will explore potential methods to mitigate these variabilities.^13^^,^^14^ We expect that patterns indicative of cardiovascular disease become apparent within a timeframe of minutes, hours, or more, considering that consumer-grade wearables have a slower sampling rate compared to the gold standard. We have shown 1 example of such a pattern: the acceleration-deceleration curve. Preselecting windows based on such patterns furthermore mitigates searching through substantial amounts of data that may not provide much information about cardiovascular disease. Inspecting the cross-correlation for several combinations of window size and lag show a different profile for healthy and AF group individuals, showing that it is meaningful to analyze step counter and heart rate together. Big data for heart disease detection requires substantial labeling efforts from physicians.

Using self-supervised learning and MIL, a model can be trained with much fewer labels. Our findings demonstrate this by employing MILES to achieve high specificity, which can aid in ruling out heart disease in individuals experiencing symptoms similar to heart disease but without the condition (ie, false-positives).

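### A different heart rate–step correlation profile in AF does not by itself show that joint analysis is meaningful, because walking pattern alone could change the profile

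*Protocol article*

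**What the plan says.** The Results section on step counter and heart rate states its question: "we examined whether the cross-correlation function between the heart rate window and its corresponding step counter window is indicative of heart disease". Its method varies two things only: "we consider varying window sizes and time differences (lags) between heart rate and steps". The one numerical finding is the delay; the matrix "shows that the heart rate is correlated with the step counter with 1-minute delay". No coefficient, interval or group contrast is given in the text. The Figure 7 caption describes "Cross-correlation matrices between windowed heart rate data and number of steps for healthy and the persistent atrial fibrillation (AF) group".

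Two conclusions are drawn. The Discussion says that the matrices "show a different profile for healthy and AF group individuals, showing that it is meaningful to analyze step counter and heart rate together". The Abstract says "we identified heart rate recovery curves and time-delayed correlations between heart rate and step count as potential strong indicators for heart disease".

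The other preliminary analysis is handled differently. The recovery curves in Figure 6 are limited to a low step range, "defined by a maximum of 20 steps in the 5 minutes preceding the peak and fewer than 10 steps in the 15 minutes after the" same point. No such limit is described for the cross-correlation.

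**The concern.** The question is whether the relation between heart rate and steps carries information on disease. The statistic compared is a correlation, which mixes three things: the heart rate response per step, the spread of step counts in the window, and the heart rate variation that steps do not explain. A group difference in any of the three changes the profile.

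Different walking habits are plausible here. In Table 1, 17 of 22 AF participants (77%) and 1 of 25 reference participants (4%) are 65 or older; 0 of 22 and 16 of 25 (64%) are aged 18–39. The reference group is by definition free of medical history and medication.

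At stake is what the preliminary result supports. If the profile partly reflects activity, it may separate older patients from younger volunteers without reflecting an abnormal heart rate response. Leave-p-subjects-out validation would not reveal this, because held-out subjects come from the same groups.

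**Working it through.** The article states no coefficient for this comparison, so there is no figure to reproduce. The check asks whether the statistic can move when the heart rate response does not.

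**1. Algebra.** Let heart rate at minute t equal a + b × steps at minute t−1 + e, with step SD S and residual SD E. Then

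r = bS / √(b²S² + E²), so r²/(1 − r²) = b²S²/E².

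Keep b and the lag the same in both groups. Let q be the AF-to-healthy ratio of step SDs, m the ratio of residual SDs, and c = q/m. Then

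r′ = c·r / √(c²r² + 1 − r²).

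With equal residual SD (m = 1, an assumption), c = q. The healthy r and q are also assumed, because the article gives neither:

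| Healthy r | q = 0.75 | q = 0.50 | q = 0.25 |
|---|---|---|---|
| 0.40 | 0.31 | 0.21 | 0.11 |
| 0.50 | 0.40 | 0.28 | 0.14 |
| 0.60 | 0.49 | 0.35 | 0.18 |
| 0.80 | 0.71 | 0.55 | 0.32 |

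Example: r = 0.60 and q = 0.50 give 0.30/√(0.09 + 0.64) = 0.35. At a lag where the correlation is zero, nothing changes.

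**2. The direction is not fixed.** Residual variation may differ as well. With r = 0.50, q = 0.6 and m = 0.5, c = 1.2 and r′ = 0.60/√(0.36 + 0.75) = 0.57. The correlation rises although step variation is lower.

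**3. Shape of the profile.** A minute-level simulation used one heart rate response throughout (0.3 bpm per step/min, 1-minute lag, autoregressive noise of SD 8 bpm, 60-minute windows) and changed only the walking pattern. The baseline had 5-minute bouts at 90 steps/min, about 20 minutes apart. All these values are assumptions.

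| Walking pattern | Within-window r, lag 1 | Lag 0 | Lag 3 | r pooled over all minutes, lag 1 |
|---|---|---|---|---|
| Baseline | 0.81 | 0.55 | 0.36 | 0.81 |
| Half as many bouts | 0.75 | 0.52 | 0.35 | 0.72 |
| A quarter as many | 0.72 | 0.51 | 0.35 | 0.60 |
| Shorter bouts | 0.70 | 0.27 | 0.05 | 0.70 |
| Half the cadence | 0.60 | 0.34 | 0.22 | 0.59 |
| Fewer, shorter, slower | 0.54 | 0.28 | 0.12 | 0.50 |

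Shorter bouts narrow the lag profile. Fewer bouts open a gap between 60-minute windows and the pooled series, so the window-size dimension can change too. (Windows without step variation were left out of the within-window means.) The driver is step variation within the window, not mean steps as such: halving the bouts moves the within-window value only from 0.81 to 0.75.

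**4. Would a regression slope escape the problem?** Only if the response is linear and steps are counted without error. In simulations with assumed values and an unchanged response, halving cadence moved the slope from 0.146 to 0.216 (0.216/0.146 = 1.48, +48%) when the response saturated. With a linear response and step-count error of SD 15 steps/min, it moved from 0.126 to 0.088 (0.088/0.126 = 0.70, −30%).

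**The case against.** A reader might infer that the different profile is simply what the step counter would produce, or that AF participants walked less. The documents support neither. Figure 7 is not shown in the text at hand, and the text says only that the profiles differ, not which is higher. No step totals by group are given. Table 1 covers all 62 included participants, not the 22 whose data were extracted. Equal residual variation is also an assumption: the article reports a considerably smaller spread of the rescaled light-activity curves in AF. That is a different quantity, but smaller residual variation would push the correlation up. This part of the objection stands, and the point is limited accordingly.

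A reader might also infer that the planned model will learn inactivity from this feature. The cross-correlation is not a stated input: the plan is self-supervised windows followed by multiple-instance learning, and the MILES example used peak-aligned curves with step data.

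The results are labelled preliminary and the indicators potential. That lowers the weight of the point but does not make the inference follow.

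Finally, if activity differs between groups, that is itself a reason to analyse steps with heart rate. This is true as an argument for taking activity into account. But the analysis was set up to test for an indication of disease, and the Abstract reports it as one; a profile difference due to activity would not support that.

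**Conclusion.** The inference is not supported as it stands. The statistic depends on step variation and residual heart rate variation, only window size and lag were varied, and no activity restriction or matching is described. The step limits on the recovery curves show that restriction by step count was feasible with these data. A difference in walking pattern could produce or contribute to a different profile; a real difference in heart rate response in AF could contribute as well.

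The direction and size of any activity effect in these data are unknown. The tables above show what is possible under a linear response, an assumed healthy correlation and assumed walking patterns; they do not estimate what happened. No false-positive rate is attached, because the article reports no test of this comparison and does not state how many subjects enter Figure 7. The point concerns what may be concluded from exploratory data and should be corrected; it does not undermine the study design.

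**What to change.** - **Comparison.** Repeat the Figure 7 comparison per subject, within windows matched on step total and step variance. Report step volume and step variance by group. A lagged regression slope may be added as a sensitivity analysis only, because it also depends on activity when the response is non-linear or steps are measured with error.
- **Evidence for joint analysis.** In the planned leave-p-subjects-out folds, run heart rate only, steps only and both, and rest the claim on that comparison. A condensed article may leave such detail to the full plan, so its absence is not an error, but this is the evidence that the claim needs.
- **Wording until then.** In the Discussion and the Abstract, say that the profiles differ and that activity level has not been excluded as a cause.

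The cost is some re-analysis of extracted data and two further input sets in validation already planned; no new data collection is needed. Matching leaves fewer usable windows, and the apparent group difference may shrink.

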### Planned machine learning approach

Our planned machine learning approach is tailored to operate in this setting through a 2-stage process. To learn informative patterns/features directly from the input data, despite the lack of labeled windows, the first stage involves using self-supervised learning. A commonly used self-supervised learning technique involves compressing the input windows to a lower-dimensional representation and then reconstructing the original input from this compact representation, as depicted in Figure 2b.^7^^,^^8^ Instead of reconstruction, another technique is to forecast future time points of the input data.^9^ The second stage involves multiple-instance learning (MIL). MIL, depicted in Figure 3 and more elaborately explained in Box 1, is suitable for data where a single prediction is made collectively on a group of samples (known as a “bag”) instead of predicting on individual samples (known as “instances”). MIL techniques align well with our time series data, where during the training phase only 1 label related to the subject (bag label) is known while the individual labels of the compressed windows (instance labels) remain unknown. In the testing phase the primary objective is to predict 1 clinical outcome for each subject. The key concept in MIL is that each bag of instances is labeled as positive (heart disease) if it contains a certain amount of positive instances and negative (healthy) if it contains no positive instances (only negative instances). Although traditional MIL approaches often classify a bag as positive even with just 1 positive instance, we aim to minimize false-positives by setting a threshold on the number of positive instances required to label a bag as positive. This threshold will be determined through hyperparameter tuning. Thus, instead of learning a model that predicts the cardiovascular outcome of individual instances, we are learning a model that predicts the outcome of a bag of instances.

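### The rule-out and avoided-visits claims are drawn from specificity, but in Table 2 the model misses 14 of 25 AF weeks and a negative result carries little information.

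*Protocol article*

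**What the plan says.** In the Results, under *MIL can detect healthy cardiovascular outcomes*, peak-aligned heart rate curves and step data are grouped by week, and the MILES "model is then used to classify every week as healthy or AF". Table 2 gives the four counts. The text comments that "even though the sensitivity is low, the specificity is decent", and continues: "This shows potential in avoiding unnecessary visits to a cardiologist for patients who have symptoms that are wrongly suspected to be related to heart problems".

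The Discussion takes this further. It describes MILES being used to "achieve high specificity, which can aid in ruling out heart disease in individuals experiencing symptoms similar to heart disease but without the condition". The specificity is thus called decent in the Results and high in the Discussion, with no new data in between.

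Two statements in the Methods, under *Planned machine learning approach*, bear on the point. On the unit of prediction: "In the testing phase the primary objective is to predict 1 clinical outcome for each subject". On the bag threshold: "we aim to minimize false-positives by setting a threshold on the number of positive instances required to label a bag as positive", followed by "This threshold will be determined through hyperparameter tuning".

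**The concern.** Specificity is the share of disease-free people whom the test calls negative. When the test is used, nobody knows who is disease-free. What matters to a person with a negative result is how far that result lowers the probability of disease, and this depends heavily on how many diseased people also test negative. High specificity on its own makes a positive result more informative. The article acknowledges low sensitivity and then draws a conclusion that needs high sensitivity.

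This inference is the main conclusion drawn from the only classification result in the article, so it shapes what readers think the study can deliver. It is also applied to people the data do not cover. Under *Study design and data collection*, the reference group has no medical history and takes no medication, whereas the claim concerns people with symptoms. Table 2 contrasts AF with healthy, whereas the Discussion speaks of heart disease in general.

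**Working it through.** **Inputs.** All counts come from Table 2, whose caption fixes the orientation: "with true and predicted labels shown vertically and horizontally, respectively". Rows are therefore true labels.

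- AF weeks: 11 called AF (TP), 14 called healthy (FN), total 25.
- Healthy weeks: 7 called AF (FP), 33 called healthy (TN), total 40.
- Subjects: *Study characteristics* gives 22 with extracted data (15 healthy, 7 AF).

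**The article's own description.** It gives words, not percentages, so there is no stated figure to reproduce.

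- Sensitivity = TP/(TP+FN) = 11/25 = 44.0% (exact 95% CI 24.4 to 65.1). *Low* is right.
- Specificity = TN/(TN+FP) = 33/40 = 82.5% (67.2 to 92.7). *Decent* is fair. With a lower limit of 67%, *high* is weakly supported.

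**What a negative result does.**

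- Negative likelihood ratio: LR- = (1 - sensitivity)/specificity = 0.56/0.825 = 0.68.
- Its interval by the log method: the standard error is √(1/14 - 1/25 + 1/33 - 1/40) = 0.192, so the limits are 0.679 × exp(±1.96 × 0.192) = 0.47 to 0.99. The upper limit is close to 1, the value at which the result carries no information.
- NPV = 33/47 = 70.2%. Within Table 2, a healthy call moves the probability of AF from 25/65 = 38.5% to 14/47 = 29.8%, about 9 percentage points.

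Other pre-test probabilities are assumptions, because the article gives none. Post-test odds are pre-test odds × 0.679:

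| Assumed pre-test probability | After a negative result |
|---|---|
| 10% | 7.0% |
| 20% | 14.5% |
| 30% | 22.5% |
| 50% | 40.4% |

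For scale, at specificity 82.5% an LR- of 0.2 would need sensitivity 1 - 0.2 × 0.825 = 83.5%, and an LR- of 0.1 would need 91.75%. These two LR- values are illustrations, not targets from the article.

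**What a positive result does.** LR+ = 0.44/0.175 = 2.51 (1.12 to 5.62), and PPV = 11/18 = 61%. The positive call is more informative than the negative one, but still weak.

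**If the table were transposed.** Reading it against its caption gives sensitivity 11/18 = 61.1%, specificity 33/47 = 70.2% and LR- = (7/18)/(33/47) = 0.55 (0.30 to 1.02). The conclusion does not depend on the orientation.

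**Clustering.** If all 22 subjects contributed, 65 weeks is about 3 per subject (25/7 = 3.6 for AF, 40/15 = 2.7 for healthy). All the intervals above treat weeks as independent and are too narrow if weeks from one person resemble each other. The article gives no within-subject correlation, so I put no figure on the widening.

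**Tuning direction.** For a fixed window classifier, requiring more positive windows before a subject is called positive cannot raise sensitivity and cannot lower specificity. This gives a direction only. The article contains nothing from which to compute a size.

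**The case against.** The strongest reply is that the limits are disclosed. The Results are labelled preliminary, all four cells are printed, low sensitivity is admitted, the caption says the classification is per week, and the Results claim only potential. A parenthesis in the Discussion mentions false positives, which suggests the authors meant sparing disease-free people a false alarm, and specificity does measure that. These points stand as context. They do not rescue the inference, because the same negative call that spares a healthy person a visit is also given to 56% of AF weeks.

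A reader might infer three stronger things, and the article supports none of them.

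- *That the planned tuning makes matters worse and the final model will fail its use.* The threshold is contrasted with the conventional rule that one positive window suffices, not with the operating point of Table 2. It is not stated to have been used for Table 2. Its value is still to be tuned, and *Algorithm validation* selects on best average performance without naming a metric. The stated objective of the study is detection; rule-out is a remark on pilot data. Sensitivity per week also does not forecast sensitivity per subject after three months of data are combined.
- *That there is a safety problem in the study.* This is an observational cohort, and nothing in the article uses model output to manage participants or cancel visits.
- *That a rule-in claim should take the place of the rule-out claim.* With LR+ 2.51 and a lower limit of 1.12, an assumed 10% pre-test probability rises only to about 22%.

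**Conclusion.** The inference from specificity to ruling out heart disease and avoiding visits is wrong on the article's own data. Sensitivity is 44%, LR- is 0.68 (0.47 to 0.99) and NPV is 70%. Whether a fall from 38.5% to 29.8% counts as small is a judgement, but it is far from ruling out. The point estimates are plain arithmetic on Table 2; only the intervals rest on treating weeks as independent. The data are silent on heart failure and on symptomatic people without disease.

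This matters for what the study may conclude. It does not undermine recruitment, data collection or the validation scheme. The aim of minimising false positives would pull against a rule-out use if that use is kept, but how much it would change sensitivity cannot be computed from the article.

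**What to change.** 1. Withdraw the rule-out statement in the Discussion and the avoided-visits statement in the Results, and say that Table 2 does not support ruling out AF.
2. Describe the specificity in the same terms in both places. Confine the comment to AF versus healthy volunteers.
3. Report sensitivity, specificity, NPV and LR- beside Table 2, with intervals that allow for several weeks per subject. State how many subjects contributed, and note that with only 7 AF subjects these intervals will be imprecise whatever method is used.
4. Decide whether rule-out is an intended use. If it is, reconcile it with the false-positive aim under *Planned machine learning approach*: choose the bag threshold in cross-validation against a pre-stated subject-level sensitivity, which the sponsor sets and justifies, and report specificity and LR- at that threshold. If it is not, drop the rule-out use and put no rule-in claim in its place.

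Items 1 to 3 cost wording and a short reanalysis. Item 4, if rule-out is kept, costs one tuning criterion and probably a lower reported specificity. At the time of the report 62 of 200 subjects were included, so the criterion could be set before the final model is chosen.
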